
## Developing and modelling the intervention:

- **0-6 months, qualitative work and development of website content.** Before a maximally effective website can be developed we need to better understand patients' perspectives. In depth semi-structured interviews with up to 30 patients will explore attitudes to infection and infection control behaviours, likely behaviour in a pandemic, as well as feasibility and process issues for the trial. We will initially use a maximum variety sample (age <65 and >65, children living in the household, gender, and social class) and perform thematic analysis; time permitting we will extend the study using techniques from grounded theory, including the selection of a theoretical sample. The semi-structured interview guide will elicit beliefs about infection; previous and current experience of hygiene measures; the perceived advantages and disadvantages of carrying out the target behaviours, and factors that would hinder or assist carrying them out; perceived social context/support; perceptions of the proposed website and the role of health professionals; and issues relevant to the process and documentation in the trial. To help us to understand the influence of family dynamics we will invite patients to include other family members in the interviews. We will show a draft version of the information we are developing for the website to patients at the end of the interview; based on the analysis of the interviews and patients' comments the information will be modified in an iterative fashion. The qualitative work will continue throughout the development phase and also in the pilot and main trials to understand issues of process and to help explain the quantitative findings (**Deliverable 1 (8 months): report of qualitative work documenting likely target attitudes and beliefs for key behaviours**)


**Pilot trial. 12-18 months: piloting and finalising the intervention.** Following the completion of the website, we will pilot the trial (i.e. invitation, intervention, and outcome measures) to confirm the extent to which the intervention can change relevant beliefs (instrumental and affective, attitudes, subjective norms, perceived behavioural control, intentions and enablement, and to confirm the acceptability/feasibility of our intervention and outcome measures. Based on previous tailored website studies we calculate that we will need a sample size of 130 per group to have 80% power to test a between-group difference (2-tailed alpha level .05). Preliminary piloting of the web pages has suggested a possible danger of demotivation if patients contract viral illnesses despite getting preventive advice regarding handwashing. To help counteract this and to support patients further we will explore in the pilot phase the impact of adding weekly messages about supporting the immune system (advice to take Echinacea use vitamin C and pelargonium^86, and the use of steam^87) in half of the intervention group. Supporting the immune system to fight infection provides a different message to avoiding transmission of viruses, and before incorporating this prior to the main trial we need to be sure that the different messages work together. By including immune system messages we will be able to examine the effect of these on hygiene

behaviours. We will also pilot methods of collection of viral samples, and compare the feasibility and acceptability of primarily postal vs. website-based outcome data collection. Further minor modifications to the website and our procedures will be made if necessary based on the findings from this pilot study. **(Deliverable 3: report on piloting (20 months) confirming change in attitudes and intentions for key behaviours.)**

**Supply of materials.** We are contacting manufacturers of alcohol based hand gels to help supply households with their product for the period of the pilot. We are estimating that it could take up to 8 weeks for some participants to complete the website sessions, and will be asking the companies for sufficient supplies to cover this timeframe. Although they will be able to provide branded products which will be displayed on the website, any branding will be removed on completion of the study. The commercial company will have access to relevant analysis from interviews and the outcome measures of the trial. However, they will not have access to individual participant information, transcripts or interview tapes. The commercial company will not have any ownership of the data collected and will have no rights to publish papers based on the information. A contract will be drawn up outlining the details of the relationship with the commercial company and this will be submitted for NRES inspection.

**Control group (normal care).** As in the intervention group, the control group will have access to the GP/practice in the normal way for respiratory illnesses and ILI (where low levels of antivirals are normally prescribed). We are not proposing to encourage all patients to access antivirals early in the illness, since the effect would be to reduce transmission rates to substantially below the rates that would be expected in a pandemic (where, even with antivirals, transmission rates are likely to be high, given the low levels of immunity and severity and duration of the illness). In our previous RCTs which have randomised at patient level (including RCTs using information leaflets) there has been little or no contamination of the control groups. In this study, since access will only be possible by a personalised password, contamination is even less likely. Inevitably some patients in the control group will want to go searching on the net for their own information, and to some extent by asking patients to participate we may increase their curiosity about such issues. We will minimise the possibility of this contamination by explicitly raising the issue prior to randomisation, and stressing the importance of a fair test of the website; we will ask patients who intend searching the web not to agree to participation; and we will minimise the incentive to do so by offering access to the website to all control patients at the end of the year. We will monitor any contamination of the control group at the end of the year of follow-up by asking all patients whether they have accessed infection control information by the web and assessing levels of key behaviours of all patients at the end of the trial to determine whether these have changed within the family. Possible contamination of the control group raises the issue of dilution of effect size, but our effect sizes are based on past trials where the sort of level of contamination possible (i.e. availability of access to information) was at least as great as in the proposed study; for example our booklet/leaflet study came at a time where the local PCTs were providing mass mailing of information booklets to many PCTs, and the companies supplying booklets were engaged in active advertising locally.

**3.4 What are the proposed practical arrangements for allocating patients to trial groups?** We propose using a very similar mechanism to our previous leaflet trial, which used a novel method to recruit large numbers of patients. 1500 patients from each practice will be identified by the practice staff with the help of research staff. If the practices would like help (the research staff will hold honorary contracts with the PCT). Letters will be sent to patients inviting them to participate. Assuming conservatively at least 66%-70% agree to the main study (we achieved an 80% uptake previously in a similar study and using a questionnaire burden that was higher than the present study) then 1000-1100 patients in each practice should agree. If fewer agree more letters will be sent out in each practice. Patients willing to participate can return the consent form directly to the research centre, or talk with the research team before replying. Those patients wanting more explanation can also attend sessions run by the practice nurse and/or research staff as appropriate. Patients will then have time to think about the study, and can also subsequently contact the research centre later before sending their consent forms back directly to the research centre. Patients can either return the consent form by post (which has previously been the case for the majority), log on to the website to confirm consent (assuming ethics approve this method). If our pilot study indicates that a primarily postal method of trial administration is needed then the trial nurse will then provide lists of patients' numbers and details in each practice to an external randomisation line (the data will include stratification variables: age >65; influenza vaccination status; size of family, children under aged 16 living at home; access to the internet; willingness of other members of the family to use the website; attendance in the previous year with respiratory infections; a skin complaint that may affect handwashing); the randomisation centre will then randomise, stratified by the above variables, and provide the randomisation lists which will be distributed to the practice staff. The practice staff will then send out separate batches of letters to intervention patients (with the personalised website password depending on which intervention they will access) and to control patients (no password). Patients consenting to the diagnostic study will be given instructions on how to take samples, and will see a nurse for demonstration as necessary. Patients will be given the symptom diary for them to complete when an ILI develops. If the pilot study indicates that a primarily website-based method of trial administration is appropriate then randomisation will be automated and outcome measures collected electronically (with paper-based follow-up of non-respondents).

**3.5 Methods of protecting against bias (e.g. masking, blinding)?** Blinding of patients to whether they have

received the intervention is impossible. Data entry will be blind to study group. Selection bias and non-response/loss to follow-up bias will be assessed by comparing the socio-demographic/clinical characteristics of those recruited/not recruited and followed up/not followed-up respectively. **Selection bias:** We will document when eligible patients are not entered into the study, the reason why, treatment, and clinical characteristics.

**3.6 Inclusion criteria.** Adult patients (aged 18+) from GPs computerised lists where there is at least another living in the household. **Exclusion criteria.** Patients with severe mental problems (e.g. major uncontrolled depression/schizophrenia;dementia;severe mental impairment - unable to complete outcomes) or terminally ill. Patients who have reported a skin complaints that may affect their ability to wash their hands. Participants who live in a household where no one else is willing to provide information on illnesses via the website.

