### **3.3 What are the planned trial interventions.**

**Infection control website.** Our key intervention will be access with a personal password to a website providing advice on infection control behaviours, with reinforcement by email reminders to use the site. A website is likely to be the most efficient and cost-effective mode of delivery in a pandemic as the majority of homes now have access to the web and the figure rises each year (National Statistics; August 2006); currently more than 60% of households have access to the web and the figure goes up year on year by 5% each year in a linear fashion - which suggests that even by the end of this trial 80-90% of families could have home access to the web. A recent US study confirmed that most people would use Google as their first source of information in a pandemic. A website will facilitate tailoring of the intervention to the individual, and personalised action planning - and thus is the most likely to be effective. Having both personalised advice via the web and behavioural prompts (regular email contacts) will provide mutual reinforcement of consistent messages. The website will be tailored to provide targeted advice based on the factors that have been shown to be important influences on behaviour in the qualitative study and survey carried out in the development phase. These are likely to include: family circumstances and lifestyle factors that may affect which behaviours are feasible and preferred (e.g. availability of suitable space to isolate infected family members, skincare problems); beliefs and concerns regarding infection transmission and control; strategies for overcoming barriers to adherence (e.g. forgetting, negotiation with other family members); current infection status of family and adherence levels (i.e. specific advice will be given when the individual or another member of the family is ill, and depending on the current level of reported adherence to each behaviour). The randomised individual (the index person) will be the main target for behaviour change which should limit spread from that person to members of the household and vice versa. However the maximum effect on illness in the family will be if all members of the household participate and change behaviour; this will be encouraged at invitation, and all members of the household will be encouraged to use the website. The extent to which it is possible to engage other members of the household, and the optimum methods for achieving this will be explored in the development phase. During the pilot, participants will be made aware that they will not be able to participate if all other members of their household refuse to provide additional information on their cold and flu illnesses. Through the website and the individual passwords

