**Main trial analysis.** The data will be analysed according to the Statistical Analysis Plan which will be approved by the Trial Steering Committee before the commencement of any analysis. One intention to treat analysis will be performed. We will assess the transmission of ILI or other respiratory tract infection - i.e. either between the index case and family members or from family members to the index person - using multiple logistic regression, the duration of symptoms labelled moderately bad days using multiple linear regression, and attendance at the GP surgery using Poisson regression, controlling for stratifiers. We found in our previous trial of leaflets there were no significant clustering effects by practice; our analysis will be based on the index patient to avoid a design effect due to family clustering. For the symptom data the main analysis will be of symptoms in the index person but a secondary analysis will assess symptoms reported for all other family members averaged at the level of the family. Confidence intervals will be reported, and the study will be reported in accordance with the CONSORT statement.

**Subgroup analysis (using two sided 1% significance levels).** We will assess whether any of the stratification variables are effect modifiers; whether age, deprivation, education level, and co-morbidities predict outcomes or are effect modifiers; whether self reported adherence to each behaviour determines outcome.

**Diagnostic study analysis.** We will assess the sensitivity specificity likelihood ratios and positive and negative predictive values for symptoms and temperature in the whole sample, and in the sub-samples who would not contact their practice or NHS Direct (either in this or in past episodes). We will use logistic regression to determine which symptoms (and or temperature) individually or in combination are most predictive. We will also estimate the predictive value of symptoms (and or temperature) for laboratory diagnosed influenza at 12 hours after the start of the illness, then at 24 hours, 36 hours, 48 hours, and 48+ hours.

**3.20 Has a pilot study been carried out?** We have not piloted this precise protocol, but have recruited very similar trial cohorts using similar recruitment mechanisms, and have developed similar websites

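### Two adults from one household can be enrolled and randomised to opposite arms of a household-directed intervention, which exposes controls and dilutes the effect

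*Protocol*

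**What the plan says.** - **Eligibility.** Protocol 3.6 admits "Adult patients (aged 18+) from GPs computerised lists where there is at least another living in the household". The exclusions cover mental and terminal illness, skin complaints, and households where nobody else will report illness. None limits how many people may join from one home.
- **Invitation.** Under 3.4, "1500 patients from each practice will be identified by the practice staff with the help of research staff". The method of selection and the list size are not given. If uptake is low, "If fewer agree more letters will be sent out in each practice".
- **Allocation.** Randomisation is by patient: "the randomisation centre will then randomise, stratified by the above variables, and provide the randomisation lists". Family size is a stratifier, but household identity and address are not.
- **Reach of the intervention.** Section 3.3 calls the randomised individual the index person and the main target for change. It expects the largest effect when the whole household takes part, and says "all members of the household will be encouraged to use the website".
- **Contamination.** The control-group paragraph in 3.3 relies on the personal password and asks people who plan to search the web not to join. It offers controls access afterwards and monitors behaviour at the end of the year. It does not discuss a control who lives with an intervention participant.
- **Analysis.** Section 3.17-.18 states that "our analysis will be based on the index patient to avoid a design effect due to family clustering".

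**The concern.** Followed as written, these rules let two partners on the same practice list both be invited, both consent and each be randomised. In about half of such pairs the arms differ. The control in that home is then one of the household members whom the intervention sets out to reach. That person can use the website through the partner and lives with the household's changed hygiene. A password controls access by strangers, not what happens inside a home.

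The contrast between arms shrinks on the primary outcome, transmission within the family. One transmission event between co-enrolled partners can also be reported by both of them, possibly in opposite arms, so outcomes are not strictly independent. Contamination that arises at recruitment cannot be undone in the analysis.

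**Working it through.** **1. Reproduce the planned sample size.** Inputs from 3.12 and its table: 20% vs 16%, two-sided 5%, 80% power, 24% of participants with transmission possible, 20% loss. I assume equal groups, since the table gives one N per group.

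- The standard two-proportion formula (pooled variance under the null, no continuity correction) gives 1447 per group, as stated.
- Total = 2 × 1447 / 0.24 / 0.80 = 15,073, against 15,074 stated.
- At 16,000 the evaluable number per arm is 16,000 × 0.80 × 0.24 / 2 = 1536. Power is 82.3%, so the margin over 80% is 2.3 points.

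**2. Set up the dilution.** Let f be the share of participants with a co-enrolled household member. **The documents do not give f, so it is assumed.** With independent 1:1 allocation of pairs, f/2 of controls live with an intervention participant. Let c be the fraction of the effect that reaches them. Contamination lowers the control rate:

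  control rate = 0.20 − 0.04 × (f/2) × c, with the intervention rate held at 0.16.

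Example: f = 20%, c = 1 gives 0.20 − 0.04 × 0.10 = 0.196, a difference of 3.6 points instead of 4.

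**3. Power at 16,000 (1536 evaluable per arm).**

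| f (assumed) | Full carry-over: control rate | Power | Half carry-over: control rate | Power |
|---|---|---|---|---|
| 0 | 20.0% | 82.3% | 20.0% | 82.3% |
| 5% | 19.9% | 80.4% | 19.95% | 81.4% |
| 10% | 19.8% | 78.5% | 19.9% | 80.4% |
| 20% | 19.6% | 74.2% | 19.8% | 78.5% |
| 34% | 19.32% | 67.5% | 19.66% | 75.5% |

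The margin over 80% is nearly used up at f = 5% with full carry-over, or at f = 10% with half.

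**4. What f might be.** Section 3.4 gives 1500 invitations and the uptake ("Assuming conservatively at least 66%-70% agree to the main study"). Assume random selection, independent consent, a partner on the same list, and an adult list of 5000 to 8000 (also assumed). Then f runs from 1500/8000 × 0.66 = 12% to 1500/5000 × 0.66 = 20%. Couples who decide together would raise it. The 34% row corresponds to inviting half of the eligible adults at 67% uptake (0.50 × 0.67). It is an upper illustration with no support in the documents.

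**5. Does the clustering break the test?** I simulated 3,072 evaluable participants (2 × 1536) with a 20% event rate, no effect, independent individual randomisation and an ordinary two-proportion test. With 20%, 34% or 100% of participants in co-enrolled pairs and within-pair correlation of 0.5 or 1.0, type I error was 4.8% to 5.2%. Correlation inflates the variance of the arm difference in same-arm pairs and reduces it in opposite-arm pairs, and the two roughly cancel.

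**The case against.** The strongest reply is that the plan's structure presumes one index person per household. Section 3.3 contrasts that person with the other household members, cohabitants are given the role of illness informants, and 3.17-.18 separates index symptoms from those of other family members. That is a fair reading of the intent. However, the term names a role and sets no enrolment rule: a couple who both consent become two index persons.

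Second, the control-group paragraph recognises contamination, argues that the assumed effect already allows for some, and plans to monitor it. That stands as far as it goes. The allowance concerns access to information, not living in a treated household, and monitoring detects exposure but does not prevent it.

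Third, a reader might infer that couples **will** both be invited. The text supports only that they can be, because the selection method and list size are not stated.

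Fourth, a reader might infer that double reporting and within-household correlation invalidate the primary test. The simulation does not bear this out under independent individual randomisation.

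Fifth, full carry-over is a worst case, because the randomised individual remains the main target for change. The half carry-over column shows the milder case.

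**Conclusion.** The gap is real. Sections 3.4 and 3.6 permit co-resident participants in opposite arms, 3.3 makes the control in such a home an intended recipient of the intervention, and nothing in the protocol prevents it. The main consequence is dilution towards no effect, which lowers the chance of detecting a true benefit but does not create false positives. The clustering statement in 3.17-.18 depends on a one-per-household condition that the protocol never sets. That is an imprecision to correct, not a cause of an invalid test.

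The size is a range, not an estimate. It rests on an assumed co-enrolment share, equal allocation, pairs randomised independently and an assumed carry-over. For co-enrolment of 10% to 20%, power at 16,000 is 78.5% to 74.2% with full carry-over and 80.4% to 78.5% with half. This should be fixed before recruitment. The unknown co-enrolment share and the conservative direction of the bias argue against ranking it higher.

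**What to change.** State in 3.4 and 3.6 that at most one adult per household is invited and randomised. Carry this out by removing duplicate addresses from each practice's mailing list before letters go out, including any top-up letters, and by checking the address again at consent. Add that a second person enrolled from the same household in error takes the first person's allocation and is left out of the index-person analysis. With that rule the statement in 3.17-.18 about family clustering becomes correct and the sample-size calculation in 3.12 can stand unchanged.

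The cost is de-duplicating the mailing lists, a few more letters to other addresses and one added eligibility line. It has to be done before recruitment, because households split between arms cannot be repaired afterwards.
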